#### 4.4 Sample size calculation

In the retrospective study by Wendrich et al., out of 112 patients 30.4% experienced CDLT (meaning compliance to chemotherapy regimen was 69.6%). Using a cut-off 43.2 cm^2/m^2, 54.5% patients had low SMM. Patients with low SMM experienced CDLT more frequently than patients with normal SMM (44.3% vs. 13.7%,  $p < 0.001$ ). Thus compliance rates to chemotherapy regimen were 55.7% and 86.3%, respectively. We hypothesize therefore that in patients with low skeletal muscle mass and weekly low dose cisplatin, also 86.3% compliance will be reached. If we compare this compliance to an expected compliance of 55.7% in the arm of with a three-weekly high dose cisplatin, 33 patients with low SMM per arm are needed to show that the compliance in the weekly low dose cisplatin scheme is statistically significantly better than the threeweekly high dose scheme (two-sided alpha 0.05 and power 80%). With an expected drop-out of 5% 70 patients with low SMM are needed. Power calculations were done using PASS software. Since 54.5% of patients undergoing cisplatin based concurrent CRT have low SMM, to find the 70 patients with low SMM a total of 129 LA-HNSCC patients undergoing cisplatin based concurrent CRT are needed.

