## 10. STATISTICAL ANALYSIS

Categorical data will be represented as a number and percentage of the total. Data analysis will be performed using statistical software R and SPSS Statistics. A test for normality (Kolmogorov-Smirnoff test) and histograms will be used to assess whether continuous variables are normally distributed. Continuous data will be represented as mean  $\pm$  standard deviation (SD) if normally distributed, and median  $\pm$  interquartile range (IQR) if skewed. Fisher's exact tests, Pearson Chi square tests, independent sample t-tests and Mann-Whitney U tests will be used to assess group differences. All analyses will be two-sided and  $p < 0.05$  is considered significant. Missing data will be handled using multiple imputation, if needed; we only expect few missing data to occur due to the nature and scale of the study.

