### 10.1 Primary study parameter(s)

The primary outcome parameter is compliance (non CDLT) rate to the proposed cisplatin scheme in the intention-to-treat population.

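### The primary compliance comparison is left unadjusted for baseline SMM; adjusting would add 0 to about 4 points of power at almost no cost

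*Protocol*

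**What the plan says.** - **Tests (section 10).** One general sentence covers all outcomes. It opens with Fisher's exact tests and continues "Pearson Chi square tests, independent sample t-tests and Mann-Whitney U tests will be used to assess group differences". The two that suit a binary outcome, Fisher and Pearson chi-square, are unadjusted.
- **Primary analysis (10.1).** The parameter is "compliance (non CDLT) rate to the proposed cisplatin scheme in the intention-to-treat population". No test, model or covariate is given. The only covariate adjustment in the protocol is the multivariate Cox model for the time-to-event outcomes in 10.2.
- **SMM and CDLT (4.4).** In the earlier retrospective cohort, "Patients with low SMM experienced CDLT more frequently than patients with normal SMM": 44.3% against 13.7%, with 54.5% of patients in the low group.
- **Use of SMM (8.3).** It is measured on pre-treatment imaging, and a cut-off decides who is randomised.
- **Randomisation (8.2).** Permuted blocks, 1:1, stratified by centre and by AJCC stage I-III against IV. SMM is not a stratum.
- **Size (4.4).** "33 patients with low SMM per arm are needed" at "two-sided alpha 0.05 and power 80"%. Then: "With an expected drop-out of 5% 70 patients with low SMM are needed".

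**The concern.** The trial rests on the premise that less muscle goes with more CDLT. Section 1 offers a possible mechanism that is graded rather than all-or-none: cisplatin may distribute mainly to fat-free mass, so less muscle may mean a higher peak. If that is right, risk still varies with SMM among the 70 randomised patients, and the value that would explain part of the variation is already on file. Leaving it out of the primary comparison leaves removable noise in a trial sized at about 80% power, with an allowance for 5% drop-out only.

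It also matters for interpretation. Treatment is open-label. If one arm happens to have lower muscle mass, the result will be questioned on that ground, and an adjustment chosen after seeing the imbalance would be post hoc.

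**Working it through.** **1. The plan's own figure.** Inputs from 4.4: compliance 55.7% (three-weekly) and 86.3% (weekly), two-sided alpha 0.05, power 80%. With mean proportion 0.71 and difference 0.306:

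n = [1.96·√(2·0.71·0.29) + 0.842·√(0.557·0.443 + 0.863·0.137)]² / 0.306² = (1.258 + 0.508)² / 0.0936 = 33.3 per arm.

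The stated 33 is therefore the size for an unadjusted two-proportion test. Dividing 66 by 0.95 gives 70. Exact binomial power of the uncorrected chi-square is 81.4% at 33 per arm and 82.8% at 35.

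**2. What explained variation is worth.** If a covariate explains a share R² of the outcome variance, the effective size is about n/(1 − R²). Putting 35/(1 − R²) into the same power formula (82.0% at R² = 0):

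| R² within low-SMM patients | Gain in power, points |
|---|---|
| 0.02 | 0.8 |
| 0.05 | 2.0 |
| 0.08 | 3.2 |
| 0.10 | 3.9 |

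**3. What R² could be.** The protocol does not say, so this is an assumption. Take SMM as normal, with 54.5% below the cut-off and a log-linear risk that reproduces 44.3% and 13.7%. The slope is then 1.085 logits per SD. Below the cut-off the SD shrinks to 0.62 of the full SD, so the slope is 1.085 × 0.62 = 0.68 per within-group SD. That gives R² of about 0.096 in the three-weekly arm.

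**4. Simulation at 35 per arm** (20,000 to 40,000 trials per row; 55.7% against 86.3%; adjusted = logistic likelihood-ratio test with linear SMM):

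| Gradient below the cut-off | Chi-square | Adjusted | Gain |
|---|---|---|---|
| 0.68 in both arms | 83.0% | 86.8% | +3.8 |
| 0.68 three-weekly, half that weekly | 82.6% | 85.1% | +2.5 |
| 0.68 three-weekly, none weekly | 82.9% | 84.2% | +1.3 |
| None in either arm | 82.9% | 83.4% | +0.5 |

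Part of this is the size of the test and not the covariate. Against an unadjusted likelihood-ratio test (84.4% in the first row, 84.3% in the last), the gain runs from +2.4 to −0.9. At 33 per arm, where the two unadjusted tests agree, it runs from +3.2 (81.4% to 84.6%) to −0.1.

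**5. The version recommended here** (marginal risk difference, robust SE, 35 per arm):
- Equal gradient in both arms: 82.9% to 85.7% in one simulation of 3,000 trials, and 81.6% to 85.9% in a second simulation. The simulation error of each power in the first is √(0.83·0.17/3000) = 0.7 points.
- Slope of 0.5 per SD: 83.2% to 83.5%.
- Weekly compliance of 80% in place of 86.3%: 60.6% to 62.9%.
- Type I error: 4.7-5.4%, against 5.2-6.0% for the likelihood-ratio test.

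A slope of 1.5 per SD would give +5.3 (82.4% to 87.7%), but it is steeper than the slope that reproduces 44.3% and 13.7%, so it is left out of the range.

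**6. Size of a chance imbalance.** A one-standard-error difference in mean SMM between arms of 35 is √(2/35) = 0.24 within-group SD. This shifts the log-odds by 0.24 × 0.68 = 0.16. At a 44.3% risk that is 0.16 × 0.443 × 0.557, about 4 points of CDLT. At 13.7% it is about 2 points.

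**The case against.** **The plan contains no error here.** An unadjusted comparison is valid in a 1:1 randomised trial and matches the sample-size calculation. The section 10 sentence is a general list, 10.1 fixes no test, and a statistical analysis plan that is not shown may hold an adjusted model. All of this stands, and it is why the point is a suggested improvement. It remains that the protocol, as written, points to unadjusted tests for the primary outcome while specifying adjustment for the time-to-event outcomes.

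**The gain rests on an unreported gradient.** This also stands. A reader might infer that the plan gives away 3 to 4 points of power. The protocol supports only a contrast between low and normal SMM, and all randomised patients lie on one side of that cut-off. If risk is a step there, the gain is nil. If weekly dosing removes the gradient in its arm, as the hypothesis of restoring compliance to the normal-SMM level could imply, the gain is about 0.5 to 1.3 points.

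**SMM is not ignored.** Restricting randomisation to low SMM already uses the one documented contrast. Only the remaining variation within that group is unused.

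**Chance imbalance is not bias.** A reader might infer that it distorts the primary result. The type I error and confidence interval of the unadjusted test already allow for it, and section 3 has baseline characteristics collected for all patients.

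**Adjustment is not entirely free.** It needs a linearity assumption and a common SMM scale. With no gradient it can cost up to about 1 point against the same unadjusted test. None of this makes it harmful.

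**Conclusion.** The point holds as an inexpensive improvement. The protocol names only unadjusted tests for a binary group difference and gives no covariate for the primary comparison, although continuous SMM is on file for every randomised patient and is not a stratum. At 35 per arm the gain is 0 to about 4 points of power. The upper end assumes a normal SMM distribution and a log-linear risk fitted to 44.3% and 13.7%, continuing below the cut-off with equal strength in both arms. The documents do not give that gradient, so no single figure inside the range can be claimed. The documents also do not support calling the planned comparison invalid or biased.

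**What to change.** In 10.1, prespecify one primary analysis: the marginal difference in compliance rate with its 95% CI, standardised from a logistic model with arm, continuous baseline SMM (one linear term) and AJCC stage group, using a robust or bootstrap standard error. Add centre only if numbers allow. Keep the unadjusted comparison as a sensitivity analysis.

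This also settles which method is primary. Section 10 lists both chi-square and Fisher, whose exact power at 35 per arm is 82.8% and 75.6%.

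Cost: a sentence or two and no new measurements. Three cautions apply:
- **Few events.** The plan's rates imply about 35 × 0.443 + 35 × 0.137 = 20 CDLT events. Keep covariates few and prefer the robust or bootstrap version to the likelihood-ratio test.
- **Linearity.** One linear SMM term is an assumption and should be stated as such.
- **Scale.** Under 4.3, patients with bilateral neck dissection can enter if an L3 scan exists, and 8.3 gives no conversion between C3 and L3. The plan must say how their SMM is put on the same scale.

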#### 8.1.2 Secondary study parameters/endpoints

Secondary outcome parameters are adverse events/toxicity, cumulative cisplatin dose, time to recurrence, 2-year overall survival, costs, quality of life and patient's preference. The main oncological outcome parameters are time to recurrence and survival. Clinically relevant treatment related toxicity parameters, including specific toxicity that results in significant (grade 3 or 4) toxicity, treatment de-escalation or termination, will be recorded by the treating medical oncologist. Toxicity will be scored according to the Common Terminology Criteria for Adverse Events (CTCAE) guidelines, v5.0.

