### 10.2 Secondary study parameter(s)

Treatment toxicity is assessed with the Common Toxicity Criteria Adverse Events (CTCAE) v5.0 for a period of 24 months from the end of treatment. Toxicity scored as CDLT by the treating physician will be assessed, clarified if necessary, and reconfirmed separately. A severe toxic event is defined as a toxicity assessed as grade 3–5. Toxicities are classified as acute if they first appeared during or up to 3 months after treatment, and are classified as late if they persist, or first appear, more than 3 months after treatment. Multiple occurrences of events of a single toxicity type within an analysis time period are counted as a single event. Median numbers of toxicity events per patient (short-term [acute] toxicity and adverse long-term [late] effects, based on the TAME method of reporting toxicities) are compared between trial arms using t-tests. Proportions of patients affected by one or more toxicity event are compared between trial arms using Fishers exact test. Total administered cisplatin dose will also be recorded and means (or medians depending on the distribution) compared between trial arms.

Overall survival, disease-specific survival, loco-regional recurrences and time to recurrence are measured from the starting date of chemotherapy and compared between the three groups by the log-rank test with all-cause mortality in the intention-to treat population. Deaths are classified as being due to head and neck cancer or to other causes. Recurrences can be loco-regional or distant, or both. Patients who died from head and neck cancer causes as the first event are classed as recurrences. Patients on follow-up and patients lost to follow-up are censored at the last date at which they were known to be alive. Total time of follow-up per patient is two years. Hazard ratios and 95% CIs are generated with a univariate Cox proportional hazards model. The Schoenfeld residuals are tested by plotting the observed Kaplan- Meier values against the Cox predicted values. The effect of randomised treatment on outcome is also assessed after adjusting for known prognostic factors with a multivariate Cox proportional hazards model. At 3 months after treatment semi-structured interviews are conducted to obtain a better understanding of the patients' experience and preference for the treatment schemes, until saturation is reached. Semi-

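### The protocol calls p < 0.05 significant for every secondary comparison, with no order or exploratory label, and its stated log-rank test includes a non-randomised group

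*Protocol*

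**What the plan says.** There is a single primary outcome (section 10.1): "The primary outcome parameter is compliance (non CDLT) rate to the proposed cisplatin scheme in the intention-to-treat population". Section 4.4 sizes the trial for that outcome alone, and section 10.4 plans no interim analysis.

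Section 10 applies one rule throughout: "All analyses will be two-sided and" a p value below 0.05 is significant. It names the tests generically: "Fisher's exact tests, Pearson Chi square tests, independent sample t-tests and Mann-Whitney U tests will be used to assess group differences".

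Section 8.1.2 lists the secondaries: "Secondary outcome parameters are adverse events/toxicity, cumulative cisplatin dose, time to recurrence, 2-year overall survival, costs, quality of life and patient's preference". It adds a partial ranking: "The main oncological outcome parameters are time to recurrence and survival". No order of testing is attached to that ranking. The quality-of-life part of 8.1.2 states that p values are unadjusted and that each time point is compared separately.

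Section 10.2 sets out the comparisons:
- Toxicity counts, described as acute and late, "are compared between trial arms using t-tests".
- Proportions of patients with any toxicity event, by Fisher's exact test.
- Total cisplatin dose, compared between arms.
- Time-to-event outcomes: "Overall survival, disease-specific survival, loco-regional recurrences and time to recurrence are measured from the starting date of chemotherapy and compared between the three groups" by log-rank test. A univariate Cox model supplies hazard ratios and 95% confidence intervals.
- An adjusted model: "The effect of randomised treatment on outcome is also assessed after adjusting for known prognostic factors with a multivariate Cox proportional hazards model".

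**The concern.** The trial is powered for compliance. Sections 11.4 and 13.2 hope for more than that: fewer adverse events, more cisplatin delivered, possibly better survival. Those are secondary outcomes, measured in 70 randomised patients. Under section 10 as written, one p value below 0.05 among many such comparisons may be reported as a significant toxicity or survival effect, with nothing to tell the reader that it was one of a large unranked set.

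The second part concerns what is tested. The section 2 objectives on recurrence and two-year survival compare the two cisplatin schedules in patients with low SMM. The log-rank test in 10.2 spans three groups. The third group is patients with normal SMM, who are not randomised and who receive their centre's standard schedule, weekly in one centre and three-weekly in the others (section 3). A significant result from that test need not say anything about the randomised schedules.

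**Working it through.** **The protocol's own figure.** Section 4.4 gives compliance of 55.7% versus 86.3%, two-sided alpha 0.05 and 80% power. With mean proportion 0.710 and difference 0.306, the pooled two-proportion formula gives

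n = [1.96 × √(2 × 0.710 × 0.290) + 0.842 × √(0.557 × 0.443 + 0.863 × 0.137)]² / 0.306² ≈ 33.3 per arm.

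That rounds up to 34, and the unpooled version gives 31. The stated 33 per arm has 79.6% power by the pooled formula. Then 66/0.95 = 69.5, so 70 patients, and 70/0.545 = 128.4, so 129. The design reproduces, and only compliance enters it.

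**Counting the secondary tests in 10.2, without quality of life.**
- Toxicity counts: 1, or 2 if acute and late are tested separately.
- Toxicity proportions: 1, or 2 if split in the same way.
- Cumulative dose: 1.
- Overall survival, disease-specific survival, loco-regional recurrence, time to recurrence: 4.

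The total is 7 on the narrowest reading, 8 with the counts split, and 9 with both split. Not counted are costs, the compliance comparison with normal-SMM patients, the adjusted Cox models and quality of life. Quality of life alone, with three instruments, four post-treatment time points and one score per instrument, would add 3 × 4 = 12.

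**Chance of at least one false positive if no secondary effect exists.** For k independent tests it is 1 − 0.95^k. For correlated tests, k equally correlated z statistics were simulated 400,000 times and each compared with ±1.96. The protocol gives no correlation, so ρ is an assumption.

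| Tests | ρ = 0 | ρ = 0.3 | ρ = 0.5 | ρ = 0.7 | ρ = 0.9 |
|---|---|---|---|---|---|
| 7 | 30.2% | 27.1% | 22.9% | 17.8% | 11.6% |
| 8 | 33.7% | 30.0% | 25.0% | 19.1% | 11.9% |
| 9 | 37.0% | 32.6% | 26.8% | 20.2% | 12.3% |

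The expected number of false positives does not depend on correlation: 7 × 0.05 = 0.35 to 9 × 0.05 = 0.45.

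Two features pull the true rate down from the independence column. First, the outcomes overlap: section 10.2 classes head and neck cancer deaths occurring as the first event as recurrences, and toxicity counts and proportions share their events. Second, Fisher's exact test at 35 per arm has an actual size of only about 1.3% to 2.8% for event rates between 30% and 90%, so the toxicity proportions contribute less than 5% each.

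**What the log-rank test addresses.** With three groups the null hypothesis is that all three curves are equal, on 3 − 1 = 2 degrees of freedom. The protocol's own rationale links low SMM to dose-limiting toxicity (44.3% versus 13.7%) and dose-limiting toxicity to shorter survival (mean 36.6 versus 54.2 months). If that holds, low-SMM and normal-SMM patients may differ in survival even when the two randomised arms do not, and the test can fall below 0.05 for that reason alone.

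**The case against.** The best reply is that ordering and alpha handling for secondaries usually sit in a statistical analysis plan, which is not at hand, and that a general p < 0.05 sentence is ordinary wording. The first half stands: the lack of a multiplicity procedure is not in itself a fault of the protocol. But the protocol does more than stay silent. It extends the significance rule to all analyses and commits to unadjusted quality-of-life p values. An analysis plan that called the secondaries exploratory would have to depart from that text.

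Other parts of the reply also stand:
- There is one primary outcome and no interim look, so the primary 5% is intact. A reader might infer that the trial's error rate rises from 5% to about 27%. The documents do not support this. The 5% is a per-test level, and no rate across secondaries is promised.
- A figure of 27% is not firm. It needs nine tests, hence the Fisher proportions split into acute and late, and an assumed correlation of 0.5. Section 10.2 attaches the acute and late split only to the event counts.
- The benefit statements are hedged. No section says that a secondary p value will support a confirmatory claim or a change of practice.
- The time-to-event methods have partly distinct roles: log-rank as the test, univariate Cox for estimates, adjusted Cox as a supplement. A reader might infer that any of several p values could be picked freely, but that goes too far. The adjusted model does refer to randomised treatment.

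This last reply does not rescue the log-rank test, which is explicitly a three-group comparison.

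**Conclusion.** The concern holds in moderate form. The protocol fixes a blanket significance rule and applies it to seven to nine secondary comparisons outside quality of life, without order or label. If every secondary effect is null, the chance of at least one significant result is 11.6% to 37.0% across assumed correlations of 0.9 to 0, and 22.9% to 26.8% at 0.5. The upper end requires independence, which these overlapping outcomes will not have. Every value in the range is more than twice the per-test level.

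The firmest element needs no assumed correlation: the stated log-rank test includes a non-randomised group and so does not answer the two-arm objectives. Disease-specific survival and loco-regional recurrence are also tested in 10.2 without appearing among the secondary outcomes in sections 2 and 8.1.2.

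None of this touches the validity of the primary analysis. It affects how secondary results may be described.

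**What to change.** - **Section 10:** limit the rule that p < 0.05 is significant to the randomised two-arm comparison of compliance.
- **Sections 8.1.2 and 10.2:** label all secondary comparisons exploratory, including quality of life, disease-specific survival and loco-regional recurrence. Report effect estimates with 95% confidence intervals and describe any p values as nominal.
- **Section 10.2, time-to-event outcomes:** for each, name one two-arm analysis in the randomised low-SMM patients as the reported result, for example the two-arm log-rank test with its Cox hazard ratio. Make the adjusted Cox model a sensitivity analysis and the three-group comparison descriptive.

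If the sponsor wants a confirmatory claim on a secondary outcome, a fixed testing sequence or a Bonferroni split (0.05/7 = 0.0071 or 0.05/9 = 0.0056 per test) would have to be written in before the data are seen.

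The cost is a few sentences, with no extra patients or data. The price is that secondary results can no longer be called statistically significant.

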### 10.1 Primary study parameter(s)

The primary outcome parameter is compliance (non CDLT) rate to the proposed cisplatin scheme in the intention-to-treat population.

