
A retrospective study in patients with LA-HNSCC undergoing CRT with three-weekly cisplatin found an association between low skeletal muscle mass (SMM) and the occurrence of cisplatin dose limiting toxicity (CDLT). Total (whole body) SMM can reliably be estimated based on measurement of the cross-sectional area of the sternocleidomastoid muscle and paravertebral muscles on the level of the third cervical vertebrae (C3) on routinely performed CT or MRI. This method has been validated and appeared to be robust when comparing it to the common method measuring the muscle area at the level of the third lumbar vertebrae (L3). CDLT was defined as cisplatin induced toxicity causing either  $\geq 4$  days postponement of the treatment,  $\geq 50\%$  dose-reduction or termination of therapy before the third cycle. Patients with low SMM were more than three times more likely to develop CDLT compared to patients with normal SMM (44.3% vs. 13.7%); consequently, compliance (no CDLT) rate to planned chemotherapy scheme was 55.7% and 86.3%. Moreover, patients experiencing CDLT had

a lower overall survival than patients who did not (mean 36.6 vs. 54.2 months,  $p = 0.038$ ). Cisplatin possibly distributes mainly to the fat-free mass, of which SMM is the largest component, and thereby a higher and more toxic peak dosage might be reached in patients with low SMM receiving high dose cisplatin. Since early discontinuation of therapy automatically leads to a reduced cumulative cisplatin dose, which is associated with lower overall survival, it can be anticipated that particularly patients with low SMM might benefit from weekly low dose cisplatin based concurrent CRT to achieve an adequate cumulative dose comparable to patients with normal SMM. In this multicenter prospective randomised low intervention clinical trial, we aim to investigate if weekly low dose cisplatin can increase the compliance to the planned chemotherapy scheme in patients with low SMM to a level of compliance to three-weekly high dose cisplatin of patients without low SMM.

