## 8. METHODS

### 8.1 Study parameters/endpoints

#### 8.1.1 Main study parameter/endpoint

The primary outcome parameter is compliance (non CDLT) rate to the proposed cisplatin scheme. Compliance to chemotherapy is defined as the absence of CDLT. CDLT is defined as any toxicity resulting in a cisplatin dose-reduction of  $\geq 50\%$ , a postponement of treatment of  $\geq 4$  days or a definite termination of cisplatin after the first or second cycle of therapy. For weekly cisplatin regimens CDLT is defined as skipped cisplatin treatments or a definite termination of cisplatin before all scheduled cycles of therapy are given.

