#### 8.4.1 Specific criteria for withdrawal (if applicable)

- The patient or its legal representative request that the patient will be withdrawn from the study.

- The sponsor decides to discontinue the study due to significant safety or efficacy concerns.
- The patient becomes pregnant.
- The treating physician withdraws the patient from the study. This decision can be made because of progressive disease, toxicity or patient's inability to be exposed to the study treatment. Since early termination is one of the outcomes of this study, we will not exclude the patient from data-analysis if not explicitly requested by the patient or treating physician.

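### Compliance is defined only as absence of CDLT, so a randomised three-weekly patient who never starts cisplatin counts as compliant, while early termination in the weekly arm does not

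*Protocol*

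**What the plan says.** Protocol 8.1.1 fixes the endpoint: "Compliance to chemotherapy is defined as the absence of CDLT". The general rule, which covers the three-weekly schedule, begins "CDLT is defined as any toxicity resulting in a cisplatin dose-reduction of" at least 50%, adds a delay of at least 4 days, and ends with "a definite termination of cisplatin after the first or second cycle of therapy". The weekly schedule has its own rule: "For weekly cisplatin regimens CDLT is defined as skipped cisplatin treatments or a definite termination of cisplatin before all scheduled cycles of therapy are given".

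Section 10.1 applies the endpoint to everyone randomised: "The primary outcome parameter is compliance (non CDLT) rate to the proposed cisplatin scheme in the intention-to-treat population".

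Section 1 describes CDLT in the retrospective study that supplies the planning rates: "CDLT was defined as cisplatin induced toxicity causing either" a delay, a reduction or early termination.

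Section 8.4.1 foresees withdrawal for progression or inability to receive treatment as well as for toxicity, and says of withdrawn patients: "we will not exclude the patient from data-analysis if not explicitly requested by the patient or treating physician".

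Section 4.4 plans on 55.7% compliance in the three-weekly arm and 86.3% in the weekly arm, with 33 patients per arm, and continues: "With an expected drop-out of 5% 70 patients with low SMM are needed".

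**The concern.** The trial asks whether patients receive the planned cisplatin. Sections 1 and 13.2 give the reason: an incomplete scheme lowers the cumulative dose, which is linked to survival. An endpoint that looks only for toxicity-driven events cannot detect non-completion for other reasons. Under intention-to-treat, a three-weekly patient given no cisplatin falls on the success side.

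The weekly rule is written differently and does detect such stops, so the same course of events is scored in opposite ways in the two arms. Allocation is open (Section 8.2), so refusal may also depend on the arm. At stake is the primary comparison: the observed difference shrinks, and a real weekly advantage may be missed.

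**Working it through.** **1. Classifying patients under the text as written**

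| Course of events | Three-weekly | Weekly |
|---|---|---|
| Never starts cisplatin | No toxicity, and no stop after cycle 1 or 2: compliant | Scheduled doses not given: taken here as non-compliant |
| Stops early for refusal, progression or unrelated death | Compliant, if toxicity must cause the stop | Stopped before all scheduled cycles: non-compliant |
| Stops early for toxicity | Non-compliant | Non-compliant |

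The first three-weekly cell holds however 8.1.1 is parsed. The second depends on whether toxicity governs the whole list or only the dose reduction. Section 1 uses the causal form for all three limbs, which supports the first parsing without making it certain.

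**2. Reproducing the planned size**

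Inputs from Section 4.4: p1 = 0.557, p2 = 0.863, two-sided alpha 0.05, power 80%. Allocation is 1:1 (Section 8.2).

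n = [1.96·√(2·0.71·0.29) + 0.8416·√(0.557·0.443 + 0.863·0.137)]² / 0.306² = 33.3, so 34 per arm against 33 stated. Power at 33 per arm is 79.6%. Drop-out: 66/0.95 = 69.5, so 70, or 35 per arm. The sample size arithmetic is sound. With 35 per arm analysed, power is 82%.

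**3. Effect of the rule as written**

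Let q be the share who never start or who stop without toxicity. The protocol gives no value, so q is an assumption. It is taken as equal in both arms, with the planned rates in everyone else.

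- Three-weekly: 0.557(1 − q) + q
- Weekly: 0.863(1 − q)
- Difference: 0.306(1 − q) − q

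Example at q = 5%: 0.557 × 0.95 + 0.05 = 57.9%; 0.863 × 0.95 = 82.0%; difference 24.1 points.

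**4. Effect of one any-cause rule**

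- Three-weekly: 0.557(1 − q)
- Weekly: 0.863(1 − q)
- Difference: 0.306(1 − q)

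| q | As written | Difference, power | Any-cause rule | Difference, power |
|---|---|---|---|---|
| 0 | 55.7% vs 86.3% | 30.6 points, 82% | 55.7% vs 86.3% | 30.6 points, 82% |
| 3% | 57.0% vs 83.7% | 26.7 points, 69% | 54.0% vs 83.7% | 29.7 points, 78% |
| 5% | 57.9% vs 82.0% | 24.1 points, 60% | 52.9% vs 82.0% | 29.1 points, 75% |
| 10% | 60.1% vs 77.7% | 17.5 points, 35% | 50.1% vs 77.7% | 27.5 points, 68% |

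Power is for the two-proportion test with pooled variance at 35 per arm. The two differences are exactly q apart. That gap is the part due to scoring the arms differently; the rest of the loss comes from counting non-toxicity stops in the weekly arm at all.

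**The case against.** **The protocol nowhere says in words that non-starters are compliant.** The case against is that this is silence, of the kind usually left to a statistical analysis plan, and that the drop-out allowance, exclusion on request (8.4.1) and multiple imputation (Section 10) are other routes. This does not hold. Sections 8.1.1 and 10.1 fix both definition and population, and together they assign these patients an outcome. Section 8.4.1 retains withdrawn patients by default. Neither the drop-out allowance nor the imputation sentence puts them in another class.

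**Stops after cycle 1 or 2 depend on parsing.** This stands. If toxicity governs only the dose reduction, a stop after cycle 1 or 2 for any reason is CDLT. Never starting still escapes.

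**The weekly rule may be meant to require toxicity too, since it defines a dose-limiting toxicity.** Its wording does not say so. If it did, such patients would be compliant in both arms: at q = 5%, 57.9% vs 87.0%, 29.1 points and 79% power. The imbalance would go, but patients given no cisplatin would still count as successes.

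**Stronger readings that the protocol does not support.** A reader might take the 5% drop-out as the rate of affected patients, giving 0.05 × 35 = 1.75 per arm. Section 4.4 does not say what drop-out covers, and weekly terminations are already non-compliant. A reader might also count 1/35 = 2.9 points per patient, so 5.7 points for two, and set that against the planned 30.6. That compares with scoring those patients as failures; against the planned 55.7%, two patients add 2 × 0.443/35 = 2.5 points. Nor does the rule favour a false claim for the weekly schedule: with equal shares it works the other way.

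**Mitigation.** Sections 4.2 and 4.3 admit only patients planned for cisplatin and without an absolute contraindication to it or to the three-weekly schedule, so non-starters may be few. Section 10.2 compares total administered dose, so a zero-dose patient remains visible there. Both points limit the size; neither corrects the primary endpoint.

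**Conclusion.** The point holds for three-weekly patients who never start, under either parsing of 8.1.1. For three-weekly patients who stop after cycle 1 or 2 without toxicity, it holds on the causal reading. Because the weekly rule states no toxicity condition, the misclassification differs by arm and is directed against the weekly schedule.

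Its size depends on a rate that the protocol does not give. Over an assumed 3% to 10%, the difference falls from 30.6 points to between 26.7 and 17.5, and power from 82% to between 69% and 35%. The share due to unequal scoring is the distance from the any-cause column: at 5%, 5.0 points of difference and 15 points of power (75% against 60%). These figures assume equal shares in both arms, 35 per arm, the planned rates in all other patients, and weekly non-starters counted as non-compliant. The planned sample size itself reproduces and is not in question.

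**What to change.** In 8.1.1 and 10.1, state one rule for both arms: a randomised patient who does not start, or does not complete, the allocated cisplatin scheme for any reason counts as non-compliant in the intention-to-treat analysis. Keep toxicity-caused CDLT, defined alike in both arms, as a supportive analysis, with the reason for stopping recorded. Make the change together with any repair of the differing CDLT definitions between schedules.

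The text change is small, and the data are already planned: CDLT, toxicity and changes of treatment strategy in Section 8.3, total dose in Section 10.2. It alters outcome classification only, not treatment.

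The cost is statistical. The 55.7% and 86.3% come from a toxicity-based definition, so any-cause rates will be somewhat lower, and the stated power should be recalculated. At 35 per arm it would be 78%, 75% and 68% for q of 3%, 5% and 10%. By the same formula, 80% power would need 37, 40 and 47 analysed patients per arm.
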